## 4. Discussion

Here we report the rationale and design for a multi-center randomized and controlled clinical trial, which aims to demonstrate the safety and efficacy of flecainide in the prompt cardioversion of atrial fibrillation in patients with coronary artery disease and EF > 35% without residual ischemia in an ED setting. We selected amiodarone as the relational agent due to its wide adoption and known safety and efficacy profile. Vernakalant was considered as well, but its limited availability and higher cost made the comparison not feasible at this time. 

In patients without structural heart disease, the use of intravenous flecainide or propafenone is recommended, while for patients with a history of heart failure or SHD, amiodarone is the drug of choice. Vernakalant is a novel agent with a good safety profile and performance in terms of successful cardioversion in a timely fashion. In the recent post-hoc analysis of the large, international, observational SPECTRUM study [16], IV vernakalant was well-tolerated, albeit with a few (0.9%) adverse events involving significant bradycardia, including sinus arrest. Successful cardioversion was reported in 67.8% of episodes and the median length of hospital stays at the ED was 7.4 h. Vernakalant may be used in patients with a history of coronary artery disease, which is a patient group where amiodarone is typically used. However, vernakalant’s limited availability and debatable cost-effectiveness could hinder its wide adoption at the present time and should be avoided in cases of severe heart failure, hypotension or acute coronary syndrome. 

On the other hand, class IC agents, such as flecainide, are contraindicated for the cardioversion of patients with coronary artery disease post-revascularization, as well as patients with ischemic cardiomyopathy and preserved ejection fraction, although there is a literature gap in this setting [13,17,18]. At the same time, the effectiveness and safety of flecainide for the restoration of a sinus rhythm has been proven in a series of clinical trials, some of which being randomized, as well as in several meta-analyses [17,19,20]. Flecainide has been associated with a shorter cardioversion time when compared to amiodarone or propafenone, which could pave the way for early hospital discharge directly from the ED.

The main risks related to antiarrhythmic class Ic agents, including flecainide, are the negative inotropic and proarrhythmic effects. The recommendation to avoid these agents in patients with atrial fibrillation and structural heart disease with or without ischemic coronary artery disease has been based solely on the results of the CAST study performed in 1991 [21]. That study aimed to prove that the suppression of ventricular ectopy using flecainide after a myocardial infarction could lead to a reduction in the incidence of sudden cardiac death. The population was comprised of patients with a history of MI within 2 years, a reduced left ventricular ejection fraction and frequent premature ventricular contractions. The patients were segregated into three groups, where flecainide, encainide or morisizine was administered, respectively, throughout the course of the trial. However, the study faced an early termination at 10 months due to an increased mortality in patients receiving class IC agents. 

This trial, however, had several shortcomings: patients with revascularized coronary artery disease were excluded and there were no checks performed prior to the inclusion for residual ischemia or angina. Furthermore, flecainide was administered for a prolonged timespan, and not for the short time needed for the cardioversion of AF. The subsequent sub-analyses of the data of the CAST study showed that patients with angina or electric instability were more likely to have worse outcomes upon flecainide administration [22,23]. This observation could perhaps uncover the interaction between the drug and the ischemic foci as the reason for the increased mortality in these patients. It is noteworthy that the population of these sub-analyses had a non-Q myocardial infarction, which could potentially be the basis for the rejection of the hypothesis that the interaction of flecainide with the scarred substrate caused the adverse events.

The European Rythmol/Rythmonorm Atrial Fibrillation Trial (ERAFT) that followed studied the safety and efficacy of propafenon in the prevention of symptoms of paroxysmal atrial fibrillation (PAF) in patients with a history of myocardial infarction but without unstable angina nor history of ventricular arrhythmias [24]. The results were encouraging, as no increase in mortality and a frequency of ventricular arrhythmogenesis were observed during the administration of these class IC antiarrhythmic agents. 

In our recent meta-analysis [17], 473 patients with ischemic cardiomyopathy or heart failure were included and the effectiveness and safety profile of the class IC agents for the cardioversion of PAF was examined. The results showed that intravenously administered flecainide is the most effective choice for the pharmacologic cardioversion of atrial fibrillation, as only two patients needed to be treated in order to cardiovert one within 4 h. Only one patient exhibited ventricular arrhythmia in a 1992 study, 6% of patients demonstrated hypotension and 0.9% bradycardia. In studies that followed (prior to 2004), and are even referenced in the latest ESC guidelines, no episode of ventricular tachycardia was recorded. Similar results were found at the propafenone group. These findings could demonstrate that ischemia, and not the presence of structural heart disease, may be the culprit for the increased risk associated with class IC agents for the cardioversion of AF. 

In a recent retrospective study, 3445 patients receiving a class IC agent were compared to 2216 patients under sotalol or dofetilide, in a time span of 16 years [25]. The patients had variable degrees of coronary artery disease but no history of ventricular tachycardia, ICD or non-revascularized myocardial infarction. The authors found that IC agents are not associated with an increased mortality in certain patient groups that these drugs are currently restricted in, such as select patients with nonobstructive CAD without a history of VT. 

While designing the trial, patient safety was our utmost priority, and we incorporated a slew of strategies to minimize the risk for patients. First, this is evidenced by the stricter implementation of the ESC guidelines regarding residual ischemia. More specifically, in case of a CABG procedure, we required the date of the surgery to be within the last 3 years instead of 5 years. Secondly, we excluded all patients with suspicious symptoms resembling an acute coronary syndrome and we enrolled patients with a negative high-sensitive troponin result. As an extra layer of precaution, following enrolment and intervention initiation, all patients without suspicious symptoms were assessed using a second measurement of high-sensitivity troponin at 1 h. 

Furthermore, we undertook the decision to place a 24 h ECG halter device monitor, on top of the 6 h ECG monitoring at the ED, to ensure the timely detection of any adverse event that would otherwise be missed, such as PVCs, NSVT, SVT or bradycardia. As for the decision to discharge hemodynamically stable patients that have been cardioversed at 6 h, this was based on the recommendations by Dan et al. that continuous medical supervision and ECG monitoring during drug infusion and afterwards for at least half of the drug half-life is needed. Based on this, we opted to not monitor the discharged patients by other means, except from the halter device. These measures were deemed as acceptable by the National Organization for Medicines and National Ethical Committee during the approval process of this trial. 

## 5. Conclusions

We believe that the embodiment of currently restricted but more efficacious drugs in the clinical workflow for the treatment of patients with coronary artery disease, such as flecainide, could satisfy the need to reduce the length of stay at the ED and hospitalizations. Our trial aims to reappraise the role of flecainide in the cardioversion of hemodynamically stable patients, presenting to the ED without residual ischemia and an EF > 35%. Depending on the trial’s results, the trial could be extended to include all asymptomatic patients presenting to the ED with an unknown medical history, following a bedside examination and ultrasonography to exclude severe cardiac anomalies.

### Current Status

Protocol version 1.0 (27 July 2022); enrolment (recruitment) start date: 24 March 2023; projected enrolment (recruitment) completion date: 1 November 2024. Approval was granted by the National Organization for Medicines, National Ethical Committee as well as by the hospitals’ institutional review boards (IRB).

## Figures and Tables

**Figure 1 jcm-12-03961-f001:**
[figure not shown]
Screening phase flowchart.

**Figure 2 jcm-12-03961-f002:**
[figure not shown]
Intervention visit flowchart.

**Table 1 jcm-12-03961-t001:** Eligibility criteria.

Inclusion Criteria
1. Age: 18–85 years old 2. Paroxysmal Atrial Fibrillation, documented by 12-lead ECG, with one of the following: a. Atrial Fibrillation onset less than 48 h from the time of presentation to the Emergency Department b. Atrial Fibrillation onset between 48 h and 7 days from the time of presentation to the Emergency Department and if patient has been on anticoagulation for at least 30 days c. History of Coronary Artery Disease without residual ischemia, defined by one of the following criteria: ▪ PCI ≤ 1 year, or ▪ CABG ≤ 3 years, or ▪ Negative imaging-based stress testing within 1 year, and: ▪ History of known coronary artery stenosis > 60% without revascularization, or ▪ PCI ≥ 1 year, or ▪ CABG ≥ 3 years 3. Ejection Fraction > 35% (documented by cardiac ultrasound at the Emergency Department, or within 1 year) 4. Signed informed consent from the patient or legal representative.

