### 3.2. Eligibility Criteria

Patients are eligible if the duration of paroxysmal atrial fibrillation is less than 48 h at the time of cardioversion or less than 7 days with usage of NOACs for more than 30 days at the time of cardioversion. Atrial fibrillation will be confirmed with a standard 12 lead electrocardiogram (ECG). Patients will be included only if they meet strict criteria that ensures that residual ischemia is not present. More specifically, only patients with a 1 year history of PCI or 3 year history of CABG will be included. If this criterion is not met, the patients must have a negative imaging-based stress test within the previous year. Patients exhibiting angina or similar symptoms at the ED will be excluded, as is the case for patients with a history of acute coronary syndrome within the last year. Patients are eligible regardless of their EHRA symptom classification score. Patients with a history of thyroid dysfunction are not excluded. Table 1 lists the inclusion and exclusion criteria for the trial enrolment.

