**Exclusion Criteria**
1. Based on ECG at the Emergency Department: a. Atrial Flutter b. Newly documented Left Bundle Branch Block (LBBB) c. Newly documented Right Bundle Branch Block (RBBB) with QRS duration > 150 ms 2. Previously documented 24 h ECG halter monitoring with >720 polymorphic PVCs/24 h, or non sustained ventricular tachycardia 3. No history of coronary artery disease 4. Acute or within 1 year ST-Segment Elevation Myocardial Infarction (STEMI) 5. Acute or within 1 year Non-ST-Segment Elevation Myocardial Infarction (NSTEMI), according to ESC 2020 guidelines on NSTEMI: a. If troponin at t0 h is over the “low” criterion on table of the cutoff values b. If the change in troponin (Δtroponin) at t1h is over the respective cutoff value at the table for the cutoff values 6. Unstable angina, defined as myocardial ischemia at rest or at minimum effort, in the absence of acute injury/necrosis of myocardial cells 7. Known residual ischemia: a. Positive imaging-based stress testing b. Negative imaging-based stress testing ≥ 1 year, and: ▪ History of known coronary artery stenosis > 60% without revascularization, or ▪ PCI ≥ 1 year, or ▪ CABG ≥ 3 years 8. History of acute coronary syndrome within 1 year 9. Severe Aortic Valve Stenosis (mean pressure gradient > 40 mmHg, AVA < 1 cm/m^2^) 10. Severe Chronic Kidney Disease (stage ≥ 4) 11. Severe systematic disease, including neoplasmatic disease under any antineoplasmatic treatment, liver failure, infection with fever 12. Use of strategy “pill in the pocket”, by taking flecainide (max 200 mg) or propafenone (max 600 mg) within 6 h prior to Emergency Department visit 13. Known dysanexia or allergy to flecainide or amiodarone 14. Pregnancy or/and breastfeeding 15. Participation in any other clinical trial 16. Life expectancy less than 1 year 17. Inappropriate, unfit, or unwilling to follow the designated protocol procedures.

**Table 2 jcm-12-03961-t002:** Summary of type and frequency of safety and efficacy outcomes at each patient’s assessment.

Event	Screening Visit Vscr	Intervention Visit V0	Visit at 24-h (V1)	Visit at 30 Days (V2)
Type of contact	On site	On site	On site	Phone
Study phase	Screening	Intervention	Follow-up	Follow-up
Inclusion/Exclusion criteria	x			
Informed consent	x			
Demographics and medical history	x			
Physical Examination	x	x	x	
Electrocardiogram	x	x	x	
Echocardiography	x (if not within last year)		x	
Chest X-ray	x			
Laboratory Exams	x	x (1 h hs-TnI only)		

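### Table 1 makes absence of residual ischaemia an alternative to the AF-duration rule, whereas Section 3.2 requires both

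*Protocol article*

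**What the plan says.** Table 1, inclusion 2, requires "Paroxysmal Atrial Fibrillation, documented by 12-lead ECG, with one of the following". Three lettered items follow at the same level:

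- 2a: "a. Atrial Fibrillation onset less than 48 h from the time of presentation to the Emergency Department".
- 2b: onset between 48 h and 7 days, with at least 30 days on anticoagulation.
- 2c: "History of Coronary Artery Disease without residual ischemia, defined by one of the following criteria". The routes within 2c are "PCI ≤ 1 year, or ▪ CABG ≤ 3 years, or ▪ Negative imaging-based stress testing within 1 year, and", and the last route is tied to a known unrevascularised stenosis above 60%, an older PCI or an older CABG.

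Two exclusions bear on coronary status. Exclusion 3 removes patients with no history of coronary disease. Exclusion 7 removes patients with a positive imaging stress test (7a). It also removes those under 7b, "Negative imaging-based stress testing ≥ 1 year, and" followed by the same three disease conditions as in 2c.

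Section 3.2 states the AF-duration and anticoagulation rule as a requirement in its own right and then adds: "Patients will be included only if they meet strict criteria that ensures that residual ischemia is not present". It accepts recent PCI or CABG. Where that is not met, it demands a negative imaging stress test within the previous year. It names Table 1 as the list of enrolment criteria.

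**The concern.** Table 1 and Section 3.2 define different eligible populations, and the difference falls on the feature that defines the trial. The Objectives confine the safety claim to coronary disease without residual ischaemia. The Discussion suggests that ischaemia, not structural disease, may explain the risk with class Ic agents, and it lists strict handling of residual ischaemia first among the safety measures.

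Three things are at stake.

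- **Exposure.** A literal reading of the table lets patients with untested older or untreated disease be randomised to flecainide. It also lets the AF-duration and anticoagulation rule be bypassed.
- **Population.** Eligibility is settled before allocation, so the error does not by itself favour one arm. It does change the patients to whom the safety comparison applies, and the three sites could read the rule differently.
- **Per-protocol analysis.** Section 3.8 plans one. A patient who complies with Table 1 but not with Section 3.2 has no settled status in it.

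**Working it through.** The plan gives no figure to reproduce, so this is a check of the eligibility logic.

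**Rules as printed**

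- old = unrevascularised stenosis >60%, or PCI ≥1 year, or CABG ≥3 years
- c = PCI ≤1 year, or CABG ≤3 years, or (negative test within 1 year and old)
- Exclusion 7 = positive test, or (negative test ≥1 year and old)
- Table 1: (a or b or c), coronary disease present, exclusion 7 not triggered
- Section 3.2: (a or b) and c, with the same exclusions

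**Example patients** (no other exclusion applies)

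| Patient | a or b | c | Excl. 7 | Table 1 | Section 3.2 |
|---|---|---|---|---|---|
| 1. AF <48 h, PCI 3 years ago, never tested | yes | no | no | eligible | not eligible |
| 2. AF 48 h to 7 days, no anticoagulation, PCI ≤1 year, never tested | no | yes | no | eligible | not eligible |
| 3. AF <48 h, PCI ≤1 year, untreated stenosis >60%, negative test ≥1 year | yes | yes | yes (7b) | excluded | excluded |
| 4. As patient 3, but never tested | yes | yes | no | eligible | eligible |

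Patients 1 and 2 show the contradiction between table and text. Patients 3 and 4 differ only in test history, and the rules agree on each of them. That is the secondary point: an out-of-date negative test excludes, while no test at all does not.

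**All profiles**

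The categories are AF status (3: <48 h; 48 h to 7 days anticoagulated; 48 h to 7 days not anticoagulated), PCI (3: none, recent, older), CABG (3: none, recent, older), untreated stenosis (2) and stress test (4: never, negative <1 year, negative ≥1 year, positive).

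1. Coronary patterns: 3 × 3 × 2 = 18, less 1 with no coronary disease (exclusion 3) = 17. Of these, 10 include a recent PCI or CABG and 7 do not. All 7 are old. Of the 10 recent patterns, 3 are not old.
2. Not removed by exclusion 7: never tested 17, negative <1 year 17, negative ≥1 year 3, positive 0. Total 37.
3. Of those 37, meeting c: never tested 10, negative <1 year 17, negative ≥1 year 3. Total 30.
4. Table 1: 37 × 2 AF categories (a or b) + 30 entering by c alone = 74 + 30 = 104.
5. Section 3.2: 30 × 2 = 60.
6. Excess: 104 − 60 = 44. Of these, 30 are not anticoagulated at 48 h to 7 days and enter by c alone. The other (37 − 30) × 2 = 14 meet a or b without c, and all 14 are never tested.

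With item 2 limited to a or b and c made mandatory, all 44 drop out. Patient 4 remains eligible.

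The check takes the 1-year PCI and 3-year CABG histories in Section 3.2 to mean within those periods, as Table 1 does. It ignores small wording differences in how the two places describe anticoagulation and the AF clock.

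**The case against.** The strongest reply is that this is a slip in list nesting and the intended rule is plain. Section 3.2 makes both requirements mandatory, and the Objectives, Section 3.1, the Discussion and the Conclusions all describe a population without residual ischaemia. Exclusion 3 would make little sense if 2c were optional. All this is right, and it settles what was meant. It does not correct the list that Section 3.2 itself names as the enrolment criteria. The letters and the connecting words are printed, so the problem does not come from lost table layout.

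A second reply is that other safeguards narrow the exposure: exclusion of angina at the ED, of unstable angina, of infarction or acute coronary syndrome within a year and of raised troponin, and the stop on the 1 h troponin change in Section 3.5.2. These stand, but they address acute or symptomatic disease and do not test for silent residual ischaemia.

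Three stronger readings are tempting and are not supported.

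- **That the silence of exclusion 7 on never-tested patients is a separate defect of equal weight.** Once 2c is mandatory, never-tested patients without recent PCI or CABG already fail inclusion, and an exclusion need not repeat an inclusion rule. Only patient 4 remains.
- **That admitting recently revascularised patients without a stress test contradicts the text.** Table 1 and Section 3.2 agree on this, and the Discussion presents the CABG window as a deliberate tightening. Whether recent revascularisation is an adequate surrogate is a clinical judgement. The stenosis condition may also have been written only for patients never revascularised.
- **That untested patients have been enrolled, or make up some given share.** The full protocol and the eCRF check are not shown, and no document gives a frequency.

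**Conclusion.** Table 1 contradicts Section 3.2 on a rule that defines the population, and the table should not stand as printed. Applied literally, it errs in two directions: it admits patients who never meet the coronary criterion, and it admits patients who never meet the AF-duration and anticoagulation rule. The excess of 44 profiles (104 against 60) describes the logic only and must not be read as a proportion of the 200 patients.

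The mismatch between 2c and 7b for patient 4 is secondary. It is an inconsistency within Table 1, and it matters only if the stenosis condition covers a lesion left untreated in a patient revascularised elsewhere.

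**What to change.** 1. Limit inclusion 2 to 2a or 2b, and move coronary disease without residual ischaemia to a mandatory criterion of its own, as Section 3.2 already requires.
2. Make the eCRF eligibility check follow the same logic. As recruitment began on 24 March 2023, check patients already enrolled against both readings.
3. Reconcile 2c with 7b for a patient with a known unrevascularised stenosis above 60% who qualifies by recent PCI or CABG and has never been tested, and state whether the stenosis condition applies to such patients. Which clinical rule should apply is for the sponsor to decide.

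The cost is a short amendment to Table 1, an eCRF edit and a review of the patients already entered. A few fewer patients may be eligible than under a literal reading of the table.

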**Exclusion Criteria**
1. Based on ECG at the Emergency Department: a. Atrial Flutter b. Newly documented Left Bundle Branch Block (LBBB) c. Newly documented Right Bundle Branch Block (RBBB) with QRS duration > 150 ms 2. Previously documented 24 h ECG halter monitoring with >720 polymorphic PVCs/24 h, or non sustained ventricular tachycardia 3. No history of coronary artery disease 4. Acute or within 1 year ST-Segment Elevation Myocardial Infarction (STEMI) 5. Acute or within 1 year Non-ST-Segment Elevation Myocardial Infarction (NSTEMI), according to ESC 2020 guidelines on NSTEMI: a. If troponin at t0 h is over the “low” criterion on table of the cutoff values b. If the change in troponin (Δtroponin) at t1h is over the respective cutoff value at the table for the cutoff values 6. Unstable angina, defined as myocardial ischemia at rest or at minimum effort, in the absence of acute injury/necrosis of myocardial cells 7. Known residual ischemia: a. Positive imaging-based stress testing b. Negative imaging-based stress testing ≥ 1 year, and: ▪ History of known coronary artery stenosis > 60% without revascularization, or ▪ PCI ≥ 1 year, or ▪ CABG ≥ 3 years 8. History of acute coronary syndrome within 1 year 9. Severe Aortic Valve Stenosis (mean pressure gradient > 40 mmHg, AVA < 1 cm/m^2^) 10. Severe Chronic Kidney Disease (stage ≥ 4) 11. Severe systematic disease, including neoplasmatic disease under any antineoplasmatic treatment, liver failure, infection with fever 12. Use of strategy “pill in the pocket”, by taking flecainide (max 200 mg) or propafenone (max 600 mg) within 6 h prior to Emergency Department visit 13. Known dysanexia or allergy to flecainide or amiodarone 14. Pregnancy or/and breastfeeding 15. Participation in any other clinical trial 16. Life expectancy less than 1 year 17. Inappropriate, unfit, or unwilling to follow the designated protocol procedures.

**Table 2 jcm-12-03961-t002:** Summary of type and frequency of safety and efficacy outcomes at each patient’s assessment.

Event	Screening Visit Vscr	Intervention Visit V0	Visit at 24-h (V1)	Visit at 30 Days (V2)
Type of contact	On site	On site	On site	Phone
Study phase	Screening	Intervention	Follow-up	Follow-up
Inclusion/Exclusion criteria	x			
Informed consent	x			
Demographics and medical history	x			
Physical Examination	x	x	x	
Electrocardiogram	x	x	x	
Echocardiography	x (if not within last year)		x	
Chest X-ray	x			
Laboratory Exams	x	x (1 h hs-TnI only)		
24-h ECG holter monitoring		x		
Medication profile	x		x	
Adverse event assessment		x	x	x
Endpoints assessment		x	x	x

**Table 3 jcm-12-03961-t003:** Primary and Secondary Outcomes.

Primary Outcomes
The frequency of successful cardioversion to sinus rhythm [Time Frame: From the drug initiation and for 6 h] The combined frequency of premature ventricular contractions (PVCs), non-sustained ventricular tachycardia (NSVT), sustained ventricular tachycardia (SVT), bradycardia < 50 bpm and systolic blood pressure < 90 mmHg. [Time Frame: From the drug initiation and for 6 h]

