### 3.3. Randomization

Randomization is performed via an eCRF platform developed by PHARMASSIST CRO (Athens, Greece), which is also used to document all the study contacts, assessments and outcomes. 

Patients and researchers are aware of the treatment group that patients have been randomized to. The two antiarrhythmic drugs, amiodarone and flecainide, have different dosages and a different time and method of administration, making the design of a single or double-blinded trial design difficult in an Emergency Department setting. 

The process of active randomization in each of the two groups in a 1:1 ratio contributes to the prevention of selection bias and is undertaken by an independent authorized researcher who is not taking part in the rest of the trial’s procedures.

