#### 3.5.1. Screening Phase (Vscr, Emergency Department)

In Vscr, the site staff will assess eligibility according to the inclusion and exclusion criteria and obtain written informed consent. The informed consent and the whole study protocol is approved by the National Ethics Committee. Patients signing the informed consent will also explicitly consent to telephone calls by the investigators for follow-ups. A dated copy of the signed informed consent will be given to the patient. The enrolment of the participants will be considered valid once they have given their consent, completed the screening process and are deemed eligible. The moment of inclusion is defined as when the patient signs and dates the informed consent form. Any assessments and examinations related to the study are conducted after the informed consent has been obtained. Patients who sign the informed consent form also explicitly consent to telephone calls from the investigators for ongoing follow-ups.

At the ED, all patients are under continuous ECG monitoring. Once the signed informed consent has been obtained, all patients are fitted with a 24 h ECG holter monitoring device, without a removal of the ED ECG monitor. The flowchart of a patient’s baseline assessments is shown at Figure 1.

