#### 3.5.2. Intervention Visit (V0)

The intervention visit is defined as the time at which the study staff intravenously administers the assigned drug and coincides with the screening visit. The drug that will be administered to each patient will be determined randomly, through a simple randomization process, as detailed in the relevant section. Patients in both groups will remain at the ED for a total of 6 h after starting the treatment, regardless of cardioversion status. If no adverse events occur during this time, including an AV block, sinus bradycardia < 50 bpm, syncope, presyncope, or systolic blood pressure < 90 mmHg and a cardioversion to sinus rhythm is successful, the patient will be discharged. Otherwise, the patient will be admitted to the hospital. Patients receiving flecainide with an unsuccessful cardioversion at 6 h will be hospitalized and receive amiodarone. Patients with an unsuccessful drug cardioversion after 24 h will undergo electrical cardioversion, according to the clinical judgment of the attending physician. All patients (i.e., those who were discharged at 6 h following a successful cardioversion and those who were hospitalized) will be under continuous 24 h ECG halter monitoring. The hospitalized patients will also be under continuous ECG monitoring until the time of a cardioversion. The 24 h ECG halter will be removed at 24 h from drug administration initiation, regardless of the cardioversion status.

In case of hemodynamic instability during or after the administration of the drug, or if the Δ (troponin at 1 h) is above the limit of the hospital’s laboratory troponin cut-off levels, the administration of the drug will cease, and the patient will be treated according to the guidelines. At discharge, the administration or non-administration of other medication will follow the guidelines, with the exception that patients will not receive treatment with a class Ic antiarrhythmic agent. 

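### Exclusion item 5b relies on a 1-h troponin result that, as the article is written, arrives only after randomisation and drug start, so it cannot screen a patient out before dosing

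*Protocol article*

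**What the plan says.** Five places in the protocol article bear on the 1-h troponin.

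- **Table 1, exclusion item 5.** NSTEMI, acute or within a year, excludes. Part (a) uses the troponin at time zero. Part (b) applies if the change in troponin "at t1h is over the respective cutoff value at the table for the cutoff values".
- **Discussion (Section 4).** On enrolment: "we enrolled patients with a negative high-sensitive troponin result". On the second sample, presented as an added safeguard: "following enrolment and intervention initiation, all patients without suspicious symptoms were assessed using a second measurement of high-sensitivity troponin at 1 h".
- **Section 3.5.2, Intervention Visit.** A 1-h change that is too high triggers a stopping rule, which names the limit and the action in these words: "laboratory troponin cut-off levels, the administration of the drug will cease, and the patient will be treated according to the guidelines". The same section says that the intervention visit "coincides with the screening visit".
- **Section 3.5.1, Screening Phase.** "The enrolment of the participants will be considered valid once they have given their consent, completed the screening process and are deemed eligible".
- **Table 2.** The inclusion and exclusion criteria are ticked at the screening visit only. The 1-h troponin is the only laboratory test listed under the intervention visit.

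**The concern.** One laboratory result has been given two roles that cannot both hold. As an exclusion criterion it must be known before a patient is randomised and treated. As an on-treatment stopping rule it is known only afterwards.

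What is at stake is mainly patient protection. The trial gives flecainide to patients with coronary disease, and its rationale is that they have no residual ischaemia. The Discussion itself suggests that "ischemia, and not the presence of structural heart disease, may be the culprit for the increased risk associated with class IC agents". Item 5b is meant to catch the patient whose first troponin is reassuring but whose second shows an evolving infarction. If the second sample is drawn after drug start, that patient has already been exposed when the criterion is met.

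**Working it through.** The point involves no sample-size, power or error-rate figure, so there is nothing to recompute. The check is one of sequence: where each statement puts the 1-h result relative to eligibility, randomisation and dosing.

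| Place | Role of the 1-h result | Position relative to drug start |
|---|---|---|
| Table 1, item 5b | Decides eligibility | Must be before |
| Section 3.5.1 | Enrolment is valid only once eligibility is settled | Any eligibility result must be before |
| Table 2 | Criteria at screening only; 1-h troponin under the intervention visit | After, or at the same visit |
| Section 3.5.2 | Stops a drug being given | After |
| Discussion | Second sample follows enrolment and intervention start | After |

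1. **Does Table 2 settle the order?** Not alone. Section 3.5.2 says that the screening and intervention visits coincide, so a test listed under the intervention visit could in principle come before the infusion.
2. **Does Section 3.5.2 settle it?** Nearly. Administration can cease only if it has begun.
3. **Does the Discussion settle it?** Yes. It names both enrolment and the start of the intervention as preceding the second sample. Reading enrolment as mere signature of consent does not help, because intervention start is named as well.
4. **Is there a waiting rule anywhere?** No section makes randomisation or dosing wait for the 1-h result. The Discussion describes enrolment on one negative troponin.

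The sequence that results is: time-zero troponin and eligibility check, then randomisation and drug start, then the 1-h troponin. In that sequence 5a can act as a screening criterion and 5b cannot.

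**Who passes through the gap?** A patient must clear all the other filters: item 5a (time-zero troponin), item 6 (unstable angina), item 8 (acute coronary syndrome within a year), and the exclusion in Section 3.2 of angina or similar symptoms in the emergency department. What remains is an asymptomatic patient with a low first troponin and a raised 1-h change. The documents give no frequency for this.

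**The case against.** The strongest reply is that this is a slip of placement. The second troponin is clearly meant as a safeguard during treatment, Section 3.5.2 handles it properly as such, and 5b is that rule repeated in the wrong table. The order rests chiefly on one Discussion sentence, the interval from the first sample to drug start is not given, and Figures 1 and 2, which show the patient flow, are not available. Some sites may in practice have both results before dosing.

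Part of this stands. It cannot be said that no patient is ever caught before dosing, only that the text does not require it. The other exclusions also leave a narrow gap. The rest does not remove the conflict. The statements that disagree are all present in the article, so this is not a detail left to a fuller document. A figure showing the 1-h sample before dosing would contradict the Discussion and would itself call for a correction.

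A reader might also infer that patients found to meet 5b after dosing are dropped from the analysis, which would be worrying where "Patients and researchers are aware of the treatment group that patients have been randomized to". The documents do not support that. No section provides for removal, and Section 3.8 states intention to treat for all primary and secondary endpoints. It also plans per-protocol analyses, but how that population is defined is properly left to the statistical analysis plan.

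**Conclusion.** The point holds as a contradiction within the article that leaves a safety gap. As written, item 5b cannot prevent dosing, and an asymptomatic patient with a low first troponin whose NSTEMI shows only at 1 h would already have been randomised and treated. The number of such patients is unknown and probably small. This conclusion assumes that the Discussion and Section 3.5.2 describe the intended order of events. No bias in the efficacy or safety comparison is shown, and no numerical effect is claimed.

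Three further inferences are tempting and should not be drawn.

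- **That the two rules use different thresholds.** Item 5b refers to a cutoff table and Section 3.5.2 to hospital laboratory limits. The table is not reproduced in the article, so the two may be the same.
- **That the study drug itself alters the 1-h troponin.** Nothing in the document says so.
- **That the stopping rule works in the amiodarone arm only, because flecainide runs over 10 min.** This depends on when the hour starts, which is not stated. The instruction to treat according to guidelines applies to both arms in any case.

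**What to change.** **Preferred.** Keep 5b and require the time-zero and 1-h troponin results before randomisation and dosing. Amend Section 3.5.2, the Discussion and Table 2 so that the 1-h sample belongs to screening. No new test is needed, because both samples are already planned. The endpoint windows in Table 3 run from drug initiation and so do not change. The cost is up to about 1 h of delay to dosing.

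**Fallback, if that delay is not accepted.** Delete 5b from the exclusion criteria, keep 5a as the baseline troponin criterion, and keep the 1-h change as the on-treatment safety rule of Section 3.5.2. Add one sentence stating that patients who meet the rule stay in the analysis as randomised. This costs only wording. It makes the rules consistent but does not stop a patient with a rising troponin from receiving the drug, which is why it is second choice.
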